## Abstract

Aligners are the common devices used in orthodontics for the correction of malocclusion. Various materials and techniques are employed to fabricate aligners. One of those includes thermoformed and 3D aligners. These aligners can be worn for several days, and their impact on periodontal health is not known. Therefore, the aim of our protocol is to determine the effectiveness of these aligners in correcting malocclusion and their impact on periodontal health and oral microbiome. A double-blinded randomized controlled clinical trial with a total of *n* = 60 patients will be included with *n* = 30 in each group (Test: 3D printed aligners and Control: Thermoformed). The evaluation of oral health indices such as basic periodontal examination (BPE), periodontal screening and recording (PSR) that provide the status of periodontal health will be recorded. The oral microbiome assessment will be conducted with polymerase chain reaction (PCR). The primary endpoint will be the correction of malocclusion, and the secondary end point will be the status of periodontal health and oral microbiome. The duration of follow-up for each group will be 7 days for periodontal health and oral microbiome and 6 months for the space closure of 5 mm by 3D and thermoformed aligners.

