Traditionally, malocclusions are corrected with removable and fixed prosthesis appliances [4]. They bring both dental and skeletal changes resulting in the correction of malocclusions, but these have both advantages and disadvantages. They are visible, metallic, long time wearing, and lack compliance of the patients. Recently, clear aligners have been introduced for correcting intrusion, extrusion, spacing, buccolingual angulation, anterior buccal and palatal angulation, etc. [5,6,7,8]. There are different commercially thermoplastic materials to produce the clear aligners on dental models that express the tooth movement [9,10,11,12]. Both conventional fixed orthodontic treatment and aligners correct malocclusions significantly, but aligners have the advantage of correcting malocclusions by the segmented movement of the teeth and shortened duration of treatment. However, aligners have drawbacks, such as achieving good occlusal contacts, retention, and tooth torque. The evidence on the effectiveness of 3D aligners in correcting malocclusion in comparison to conventional thermoformed aligners is lacking, and a more recent update on the systematic reviews and meta-analysis in this issue is warranted [13,14,15,16,17,18]. Both therapies also have an impact on the oral microbiota and change in oral flora over a period of time. Before any 3D direct-printed aligners are adopted, 3D aligners need to be compared with traditional thermoformed aligners. To date, the dimensional accuracy of direct-printed aligners has not been tested against those of traditional thermoformed aligners. Dimensional accuracy is a common research topic in dentistry to assess dimensional precision.

A recent randomized clinical trial confirmed that treatment duration and chair time in mild-to-moderate cases appear to be significantly short over conventional systems [19]. There is also a lack of evidence on the use of aligners in space closure and its impact on periodontal health [20]. There is a need for evidence in conducting well-designed clinical trials.

The aim of the present study is to determine the effectiveness and efficacy of 3D aligners in correcting malocclusions as compared to that of thermoformed method and to determine the periodontal health status during and after 3D aligners and thermoformed aligners therapy.

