### 1.2. Aim 2: Periodontal Health Status and Oral Microbiome

The second aim is to determine the periodontal health status during and after 3D clear aligners and thermoformed aligner therapy.

Clear aligner treatment (CAT) has been described as a secure and confident orthodontic procedure for patients. Recently, adult patients have sought a more aesthetic and comfortable orthodontic treatment than fixed appliances. To meet these needs, the treatment with transparent aligners (CAT) was introduced. The clear aligners cover the keratinized gingiva for a long period of time, and it is very important from a clinical point of view that CAT does not cause negative effects on periodontal tissues. Both conventional treatment and aligners cause a shift in the increase in anaerobes and periodontal pathogens and a decrease in commensal bacteria in the supra-gingival microbiome, but there are different types of aligners, i.e., 3D aligners and thermoformed aligners that can cause a periodontal reaction due to several factors such as the presence of systemic conditions, host resistance, and the amount and composition of dental plaque. Smoking and the patient’s lifestyle can compromise periodontal health and support. Oral hygiene procedures play a primary role in periodontal health during orthodontic treatment. Therefore, the objective is to determine the status of periodontal status and oral microbiome in 3D and thermoformed CAT.

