### 2.2. Trial Design

We propose to conduct a double-blinded randomized controlled clinical trial in patients who have >5 mm of spacing in both maxilla and mandible and cases with skeletal class I coming to the department of Orthodontics and Dentofacial Orthopaedics at Fondazione IRCCS Cà Granda Ospedale Maggiore Policlinico di Milano, SST clinics and Università degli Studi di Bari and Naples Clinica Odontoiatrica. Patients in both arms will receive adhered support and will be monitored more frequently than currently recommended by WHO guidelines. The first arm will undergo a traditional method of managing of closure of spacing by thermoformed aligners, and the second aim will be treated with thermoformed and 3D printed aligners. Eligible patients are randomized to the control arm or the intervention arm with a 1:1 ratio using a blocked randomization scheme. The patients will be followed for 6 months (Figure 1).

There will be an initial assessment with detailed case history, extra-oral and intra-oral examination, and clinical radiographs. A diagnosis and treatment plan will be framed. Pre- and post-operative samples of biofilm and saliva will be collected to determine the inflammatory and immunological response. The bridging and early colonizers such as *Fusobacterium nucleatum* (*F. nucleatum)*, pathogenic species such as *Porphyromonas gingivalis (P. gingivalis)*, microbial communities and the composition of the biofilm will be determined by ELISA and PCR. This will help to answer the questions such as if any infection is present, which bacteria colonize, whether we should use antibiotics, etc. In addition, 16 s-ribosomal RNA signatures for identification of the microbial composition of biofilm structures.

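### The Abstract's 7-day window for periodontal health and oral microbiome conflicts with Aim 2, which asks about periodontal status during and after therapy, and with the 6-month follow-up in the body

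*Protocol article*

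**What the plan says.** The Abstract gives two follow-up lengths: "7 days for periodontal health and oral microbiome and 6 months for the space closure of 5 mm by 3D and thermoformed aligners".

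The objective is worded more broadly. Section 1.2 undertakes to "determine the periodontal health status during and after 3D clear aligners and thermoformed aligner therapy", and the closing paragraph of the Introduction says the same: "to determine the periodontal health status during and after 3D aligners and thermoformed aligners therapy". Section 1.2 motivates this by the long time for which aligners keep the gingiva covered. Its last sentence adds the oral microbiome to the objective, without a time frame.

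The body of the article does not repeat the 7 days. Section 2.2 says "The patients will be followed for 6 months", with no separate window for periodontal outcomes, and "Pre- and post-operative samples of biofilm and saliva will be collected", with no day or month. Section 3 plans descriptive statistics on the indices pre- and post-treatment, again undated.

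**The concern.** One of the trial's two aims rests on these outcomes. The Abstract calls them the secondary endpoint, and section 2.3 lists the hygiene, plaque, bleeding and periodontal indices, the biofilm and saliva assays and the microbiome under the primary endpoint heading. If sites work to the Abstract, the data that Aim 2 needs from the later course of treatment will not be collected, and no analysis can recover them.

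The risk lies in interpretation. Section 1.2 treats the absence of harm to periodontal tissues as clinically important. A comparison after one week of wear that shows no difference between arms could be reported as reassurance about a much longer exposure, which a one-week reading cannot give.

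**Working it through.** **The plan's own calculation.** The only calculated figure in the article is the sample size for space closure (section 3): means 3 and 5 mm, SDs 2.5 and 2.0, two-sided alpha 0.05, power 0.80.

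- Pooled SD = sqrt((2.5² + 2.0²)/2) = sqrt(5.125) = 2.264.
- The normal approximation gives 21 per group.
- The unequal-variance t-test has power 0.797 at 21 per group and 0.816 at 22.

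The stated 22 per group is reproduced. It concerns space closure only and has no bearing on the timing question. No sample size is given for the periodontal or microbiome outcomes.

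**Share of follow-up covered.** Inputs are 7 days and 6 months, both from the Abstract; section 2.2 also gives 6 months.

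- 6 months = 6 × 365.25/12 = 182.6 days.
- 7/182.6 = 3.8%. Taking 6 months as 180 or 184 days gives 3.9% or 3.8%.
- Remainder: 100% − 3.8% = 96.2%.

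This is a share of follow-up. The article gives no treatment length, so it is not a share of treatment.

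**What each reading would deliver.** The start of the 7 days is undefined and the pre/post wording is undated, so three readings are possible.

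| Reading | During therapy | After therapy | Text that must change |
|---|---|---|---|
| 7 days from aligner placement | First week only | Not observed | Aim 2 or the Abstract |
| 7 days from end of therapy | Not observed | One week | Aim 2 or the Abstract |
| Pre/post in sections 2.2 and 3 means baseline and end of treatment | No dated reading | At the end of treatment | The Abstract's 7 days |

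No reading satisfies both the Abstract and Aim 2 as written.

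**The case against.** The strongest reply is that the 7 days appear once, in an abstract, and the body never adopts them. Section 2.2 follows everyone for 6 months, and the pre/post wording in sections 2.2 and 3 can naturally be taken to mean baseline and end of treatment. An article may also leave the visit schedule to the full protocol. This stands in part: it shows that the 7-day window is not established as the operating design. It does not remove the conflict, because the complaint is about a stated duration and not a missing schedule. If end of treatment is meant, the Abstract is wrong.

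A reader might infer more than the article supports:

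- *That the trial as designed cannot answer Aim 2.* This follows only if the Abstract's window is the one applied. Counted from placement, day 7 would still fall within therapy, so that part would be thinly covered, not absent.
- *That 96% of treatment goes unobserved.* Six months is a follow-up length. Treatment length is not stated.
- *That the microbiome aim also covers both periods.* The wording about during and after therapy is attached to periodontal status only.
- *That every periodontal outcome, root resorption included, stops at day 7.* Root resorption is not named in the Abstract's sentence. Section 2.3 lists it as a separate radiographic item without a time.
- *That a day-7 comparison is bound to show nothing.* The article gives no rates of change for these outcomes, and section 2.3 describes bleeding as an early sign of inflammation.

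**Conclusion.** The concern holds as a conflict between stated rules. The only dated window for periodontal health and oral microbiome is 7 days, about 4% of the 6-month follow-up, and it matches neither the wording of Aim 2 nor the unqualified 6 months in section 2.2. If that window is applied and starts at aligner placement, only the first week is seen and the question about status during and after therapy cannot be answered. A null result would then speak to one week of wear and not to periodontal safety over the course of treatment. Both conditions are assumptions, since the article does not define the start and its undated pre/post wording allows an end-of-treatment assessment. The need to reconcile the sections does not depend on which reading is right.

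**What to change.** Before data collection, reconcile the Abstract, the Introduction, section 1.2, section 2.2 and section 3 in one of two ways.

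1. Preferred: make the 6-month follow-up already planned for space closure the main time point for the periodontal indices and for the post-treatment biofilm and saliva sample. Keep day 7 as an early descriptive reading, with its starting point defined. Put these dates in sections 2.2 and 3 and correct the Abstract. State also whether month 6 counts as the end of therapy, so that the word after in Aim 2 has a defined meaning.
2. Otherwise: keep the 7-day window, define its start, and narrow Aim 2 and every conclusion drawn from it to a 7-day effect.

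The first option adds some examination and laboratory work, unless the single post-treatment sample is moved from day 7 to month 6. It also exposes the periodontal and microbiome data to the same loss to follow-up as space closure. The second option costs nothing to run but gives up the question that section 1.2 sets out to answer.

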## 1. Introduction

The prevalence of malocclusion varies among different regions and races of the population. In the United States, the frequency of malocclusion is determined by Nutrition Examination Survey (NHANES III) and the National Health. It emerged that the percentage of adults having misaligned incisors was 65%, and the percentage of adults having crowding severe enough to interfere with function and social interactions was 15% [1]. Treatment of malocclusion has become more common among the population of United States and other developing countries. There is a sense of security that the correction of maligned teeth improves the quality of life (QoL) significantly [1]. Generally, the patients believe that it provides aesthetic, psychosocial and functional benefits. There is even an economic burden for this orthodontic problem, which affects patient’s parents and families. In addition to the treatment costs, other factors such as school absence, work and productivity loss should also be considered. Interceptive therapy for malocclusion treatment is less costly and less complicated than the traditional approach but, in some situations, do not result in comparable dental outcomes. O’Brien and colleagues (2009) have looked at the cost differences between one- and two-phase treatments [2]. The authors found that the cost will be significantly higher in two-phase treatments as compared to one-phase treatments. Deans and colleagues (2009) demonstrated the cost-effectiveness of orthodontic treatment in Europe [3] and has a significant impact on orthodontic treatment on cost. In addition to the cost, conventional orthodontic treatment for correcting malocclusions (removable and fixed) has a greater tendency to cause periodontal problems. These include gingivitis, periodontitis, gingival recession, hypertrophy, fenestrations, dehiscence, dark triangles, and interdental folds. Additionally, the formation of biofilm is the most important indicator for the initiation and progression of periodontal disease during orthodontic treatment.

Traditionally, malocclusions are corrected with removable and fixed prosthesis appliances [4]. They bring both dental and skeletal changes resulting in the correction of malocclusions, but these have both advantages and disadvantages. They are visible, metallic, long time wearing, and lack compliance of the patients. Recently, clear aligners have been introduced for correcting intrusion, extrusion, spacing, buccolingual angulation, anterior buccal and palatal angulation, etc. [5,6,7,8]. There are different commercially thermoplastic materials to produce the clear aligners on dental models that express the tooth movement [9,10,11,12]. Both conventional fixed orthodontic treatment and aligners correct malocclusions significantly, but aligners have the advantage of correcting malocclusions by the segmented movement of the teeth and shortened duration of treatment. However, aligners have drawbacks, such as achieving good occlusal contacts, retention, and tooth torque. The evidence on the effectiveness of 3D aligners in correcting malocclusion in comparison to conventional thermoformed aligners is lacking, and a more recent update on the systematic reviews and meta-analysis in this issue is warranted [13,14,15,16,17,18]. Both therapies also have an impact on the oral microbiota and change in oral flora over a period of time. Before any 3D direct-printed aligners are adopted, 3D aligners need to be compared with traditional thermoformed aligners. To date, the dimensional accuracy of direct-printed aligners has not been tested against those of traditional thermoformed aligners. Dimensional accuracy is a common research topic in dentistry to assess dimensional precision.

A recent randomized clinical trial confirmed that treatment duration and chair time in mild-to-moderate cases appear to be significantly short over conventional systems [19]. There is also a lack of evidence on the use of aligners in space closure and its impact on periodontal health [20]. There is a need for evidence in conducting well-designed clinical trials.

The aim of the present study is to determine the effectiveness and efficacy of 3D aligners in correcting malocclusions as compared to that of thermoformed method and to determine the periodontal health status during and after 3D aligners and thermoformed aligners therapy.

### 1.1. Aim 1: Effectiveness and Efficacy of Clear Aligners (Invisalign) in Correcting Malocclusions

The clear aligners were introduced in the 1940s, but due to lack of evidence and promotion, it was not widely practiced and adopted. Later, due to the development of biomaterials in dentistry and 3D technology, it became very much popular. Recently, there have been more expert opinions in favor of clear aligners, and there is a lack of evidence in correcting a wide range of malocclusions [21]. Not many studies described the effectiveness of treatment with 3D and thermoformed clear aligners and its impact on periodontal health, generating doubts among clinicians on the efficacy of the device.

Therefore, a well-designed parallel randomized controlled clinical trial will help to overcome the problem. The spacing >5 mm correcting it by using 3D clear aligners and compared with thermoformed aligners therapy.

### 1.2. Aim 2: Periodontal Health Status and Oral Microbiome

The second aim is to determine the periodontal health status during and after 3D clear aligners and thermoformed aligner therapy.

Clear aligner treatment (CAT) has been described as a secure and confident orthodontic procedure for patients. Recently, adult patients have sought a more aesthetic and comfortable orthodontic treatment than fixed appliances. To meet these needs, the treatment with transparent aligners (CAT) was introduced. The clear aligners cover the keratinized gingiva for a long period of time, and it is very important from a clinical point of view that CAT does not cause negative effects on periodontal tissues. Both conventional treatment and aligners cause a shift in the increase in anaerobes and periodontal pathogens and a decrease in commensal bacteria in the supra-gingival microbiome, but there are different types of aligners, i.e., 3D aligners and thermoformed aligners that can cause a periodontal reaction due to several factors such as the presence of systemic conditions, host resistance, and the amount and composition of dental plaque. Smoking and the patient’s lifestyle can compromise periodontal health and support. Oral hygiene procedures play a primary role in periodontal health during orthodontic treatment. Therefore, the objective is to determine the status of periodontal status and oral microbiome in 3D and thermoformed CAT.

## 2. Study Design

### 2.1. Preliminary Studies

In relation to the effectiveness and efficacy of clear aligners, there are two Randomized Clinical Trials (RCT), five prospective non-randomized and four retrospective non-randomized trials. There was moderate level of bias in these studies. The Invisalign clear aligners are good in managing spacing, anterior crowding and in adjusting marginal aligners that compare the outcome with respective of periodontal conditions and oral microbiome. We expanded this hypothesis generating the findings to design, set up and recruit patients into our randomized controlled clinical trial to prospectively test that the clear aligners are good in managing spacing and crowding and can bring down the mortality of root resorption that occurs due to traditional methods. Additionally, it helps to determine its impact on periodontal oral health by assessing the saliva and biofilm under ELISA and PCR methods.

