***Baseline information:*** (1) A Patient Measured Outcome Questionnaire (PROM) was completed to determine the impact of oral health on quality of life. The PROMs are dozens of tools that allow you to measure the important results for the patient, for example, cost, symptom relief, quality of care, improved oral health, and overall health. It is evaluated after each intervention. (2) Numerical rating scale (NRS) for measuring the pain of patients before and after the intervention. (3) Periodontal health status will be assessed by basic periodontal examination (BPE), Periodontal screening and recording index (PSR index), Basic Periodontal Examination (BPE) scores, Oral Hygiene Index simplified (OHIS), Saliva (Protease activity in saliva) to determine the immune-inflammatory processes by ELISA and biofilm by polymerase chain reaction (PCR). ***Inclusion criteria:*** The eligible cases will be identified during routine clinical visits. CAT is indicated in cases of slight crowding (1–5 mm), spacing problems (1–5 mm), deep overbites (Class II, div. 2), narrow arches requiring expansion, absolute intrusion (one or two teeth), severe crowding with the extraction of the lower incisor and molars requiring distal tipping. Contraindications are crowding and spacing problems greater than 5 mm, anterior-posterior skeletal problems greater than 2 mm, relationship discrepancies and centric occlusion, severely rotated and inclined teeth, open bite, dental extrusion cases, cases with more missing teeth and teeth with short clinical crowns.

Written informed consent will be obtained before the inclusion of the study. An entry form will be completed to determine the eligibility and to collect the baseline characteristics such as periapical radiographs, panoramic radiographs, models, casts, cephalometric tracings, CBCT scans, etc. Patients will be randomized in thermoformed and 3D clear aligners. All non-extraction cases except third molar extraction will be included. ***Exclusion criteria:*** Patients with deciduous and mixed dentition will not be included, and patients with systemic disease, developmental abnormalities, pregnant patients, mentally retarded patients and immunocompromised patients will not be included in the study.

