### 2.3. Primary End Point

Five-millimeter space closure: To determine the successful outcome of the 3D and thermoformed aligners, a 5 mm of space closure is considered a successful outcome.Debris Index: (The buccal scores) + (The lingual scores)/(Total number of examined buccal and lingual surfaces).Calculus Index: Calculus Index = (The buccal scores) + (The lingual scores)/(Total number of examined buccal and lingual surfaces).Oral Hygiene Index simplified (OHIS): OHIS estimates the extent and amount of debris and calculus present on the tooth in each quadrant of the mouth. It demonstrates the oral hygiene status of the mouth. It is estimated using the debris index and calculus index provided by Greene and vermillion (1964).Plaque Index: The plaque index estimates the amount of plaque on the tooth surface in each quadrant. 0—Absence of plaque, stain or debris; 1—plaque covering no more than 1/3rd of tooth surface; 2—subtle plaque more than 1/3rd but not more than 2/3rd; 3. Plaque cover more than 2/3rd of the tooth surface.Bleeding Index: A modified Sulcus Bleeding Index (mSBI) will be used to record the bleeding from the sulcus and to determine the inflammation, as it is the early indicator of inflammation (clinically).Basic periodontal examination index (BPE): Periodontal status will be determined using the BPE scoring.Root Resorption: Basic periodontal examination such as hard tissues will be conducted using a combination of bitewing and peri-apical radiographs following selection criteria for dental radiography guidelines.Biofilm/Saliva: Saliva (Protease activity in saliva) to determine the immune-inflammatory processes by ELISA and biofilm (protease activity) by polymerase chain reaction (PCR).Oral microbiome: A standard estimation of the oral microbiome will be carried out using 16S ribosomal RNA gene sequencing analysis.

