### 2.4. Secondary End Point

White Spot Lesions, Patient Reported Outcome Measures (PROM’s).

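### The stated hypothesis covers crowding and the aim covers malocclusion in general, but space closure is the only tooth-position outcome, so the trial can conclude on space closure alone

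*Protocol article*

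**What the plan says.** The protocol article states what it tests in three ways.

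- **Hypothesis.** Section 2.1 says patients were to be recruited "to prospectively test that the clear aligners are good in managing spacing and crowding".
- **Aim.** Section 1 closes with the aim "to determine the effectiveness and efficacy of 3D aligners in correcting malocclusions as compared to that of thermoformed method". The heading of section 1.1 (Aim 1) uses the same broad term.
- **Endpoint label.** The abstract says: "The primary endpoint will be the correction of malocclusion".

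The operative text is narrower. In section 2.3, "a 5 mm of space closure is considered a successful outcome". The other primary items there are hygiene, plaque, bleeding and periodontal indices, root resorption, saliva and biofilm, and the microbiome. Section 2.4 adds "White Spot Lesions, Patient Reported Outcome Measures". Section 3 sizes the trial on mean space closure.

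Section 2.2 describes eligibility twice. Its opening sentence refers to "patients who have >5 mm of spacing in both maxilla and mandible" and to skeletal class I. Its inclusion-criteria text says "CAT is indicated in cases of slight crowding (1–5 mm), spacing problems (1–5 mm"), followed by several other malocclusions, and it then names spacing above 5 mm as a contraindication.

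**The concern.** A trial supports a conclusion only on what it measures, in the patients it enrols. Here the hypothesis names two conditions and only one has an outcome. The aim and the abstract's endpoint name a whole class of problems, and the measured outcome is one of them.

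Two things are at stake. First, someone who reads the abstract would take a positive result as showing that one aligner type corrects malocclusion better, when the data would show only that it closes more space. Secondly, if the inclusion-criteria text is followed as it stands, patients could be randomised for crowding who have no space to close. The primary endpoint is undefined for them, and the article does not say how they would be handled.

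**Working it through.** This is a question of coverage. The sample size is the only figure that bears on it.

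**1. What the sample size rests on.** Section 3 gives means of 3 mm (control) and 5 mm (test), SDs of 2.5 and 2.0, two-sided alpha 0.05, power 0.80, 1:1 allocation, and 22 per group (44 in total) before allowance for loss to follow-up.

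- Normal approximation: n per group = (1.960 + 0.842)² × (2.5² + 2.0²) / (5 − 3)² = 7.85 × 10.25 / 4 = 20.1, rounded up to 21.
- Noncentral t with unequal SDs: power is 0.797 at 21 per group and 0.816 at 22 per group, so 22 is the smallest number that reaches 0.80.

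The stated figure reproduces, and every input is millimetres of space closed. The article gives no effect size or SD for crowding or for any general measure of malocclusion, so no power for either can be calculated.

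**2. Endpoint count.** The classification is that of the section headings.

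| Section | Items | Tooth position | Crowding or alignment |
|---|---|---|---|
| 2.3, primary | space closure; debris; calculus; OHIS; plaque; bleeding; BPE; root resorption; biofilm/saliva; microbiome (10) | 1 (space closure) | 0 |
| 2.4, secondary | white spot lesions; PROMs (2) | 0 | 0 |
| Total | 12 | 1 | 0 |

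**3. Claim against measure.**

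| Claim | Where | Outcome that could support it |
|---|---|---|
| Aligners manage spacing | 2.1 | Space closure, 2.3 |
| Aligners manage crowding | 2.1 | None |
| Malocclusion is corrected | Abstract, 1, 1.1 | Only its spacing part, through 2.3 |

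**4. Eligibility against endpoint.** The opening of section 2.2 fits a space-closure endpoint. The inclusion-criteria text does not fit it fully. A patient who enters for crowding and has no spacing has zero space available, so neither the millimetres closed nor success at 5 mm has a meaning for that patient. The two statements also disagree on spacing itself: the first describes patients above 5 mm, and the second places spacing above 5 mm among the contraindications.

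**The case against.** The best reply is that most of the narrowing is already in the article. Crowding as something to be tested appears only in section 2.1, a loosely written background paragraph. The last line of section 1.1 speaks of spacing, the abstract ties the 6-month follow-up to space closure, and sections 2.2 (opening), 2.3 and 3 all work with spacing. All of this is correct. It shows what the trial is really about and makes the correction cheap. It does not remove the mismatch, because the sentence in section 2.1 says what this trial will test, and the broad label stands in the abstract, where it will be read most. Nor is the gap a detail left to a fuller document, because the article sets out its endpoint list and success definition itself.

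Three stronger readings are tempting, and the document does not support them.

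- *The abstract promises a result on crowding.* It does not mention crowding. It names malocclusion and then narrows the follow-up to space closure.
- *A positive result may reflect only more tipping of teeth into the gap in one arm.* Section 1 does say that "aligners have drawbacks, such as achieving good occlusal contacts, retention, and tooth torque", and no endpoint records these. But that sentence concerns aligners as a class, set against fixed appliances, and both arms here are aligners. It gives no reason to expect the arms to differ. The article does not discuss tipping in relation to the endpoint, and any estimate of its size needs an assumed centre of rotation and an assumed single gap, neither of which the document gives.
- *Removing crowding from the hypothesis settles the matter.* It does not, because the inclusion-criteria text would still list crowding.

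**Conclusion.** The point holds as a mismatch between claim and measurement. None of the 12 listed endpoints addresses crowding, one addresses tooth position, and the sample size is built on that one. No result on crowding, or on malocclusion in general, can come from this trial as described. The comparison of space closure is not damaged by the mismatch, except that patients without spacing, if enrolled under the inclusion-criteria text, could not be scored on it.

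The conclusion rests on two readings. The endpoint lists in sections 2.3 and 2.4 are taken as complete. The opening of section 2.2, whose syntax is loose, is taken to mean patients who have both spacing and skeletal class I. The document does not support going further and saying that a positive space-closure result would be spurious.

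**What to change.** 1. In section 2.1, remove crowding from the hypothesis.
2. In the abstract, in the closing aim of section 1 and in section 1.1, name the aim and the primary endpoint as space closure in skeletal class I patients with spacing. State that the eventual conclusion will be limited to this.
3. In section 2.2, reconcile the opening description of patients with the inclusion-criteria text, and reconcile both with the endpoint, so that every randomised patient can be scored on it. Which spacing limits should apply is for the investigators to settle.

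Steps 1 and 2 cost only wording and a narrower claim. Step 3 needs a decision on who is eligible and may reduce the pool of candidates. None of the steps changes the endpoint, the sample size calculation or the primary analysis.

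As an option only, the investigators could describe tooth angulation and occlusal contacts at 6 months. The article lists models, tracings and CBCT scans at baseline only and does not say how space is measured, so this might need follow-up records beyond those planned. The correction does not depend on it.
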